## Methods and analysis

### Objectives

INJUSTIS is a prospective multicentre observational cohort study that will be managed through the Nottingham Respiratory Research Unit and funded by the National Institute of Health Research (NIHR) through the Nottingham Biomedical Research Centre and an NIHR professorship ([name]).

The primary objective is to:

Identify biomarkers that determine progressive fibrotic lung disease irrespective of aetiology.

The secondary objectives are to:

Identify biomarkers that predict all-cause mortality.Identify biomarkers that predict changes in QoL scores.Identify biomarkers that predict the development of disease complications (respiratory failure and acute exacerbations).Investigate genetic association and epigenetic modifications which affect fibrotic disease severity and progression.Prospectively evaluate longitudinal disease behaviour in patients with non-IPF fibrotic lung diseases with a view to developing composite clinical end points for subsequent use in intervention studies.Explore association of environmental exposures with disease progression and all-cause mortality.Investigate whether home handheld spirometry over 3 months predicts disease progression and survival.

The primary end point will be:

Disease progression defined as relative forced vital capacity decline ≥10% or death within 12 months.

Secondary end points are:

All-cause mortality at time of censoring.Number of acute exacerbations over 2 years.Change in Quality of Life (QoL) Questionnaire Scores from baseline to 12 weeks.Rate of change in biomarker activity from baseline to 12 weeks.Change in diffusing capacity of the lung for carbon monoxide (DLco) from baseline to 12 months.Change in 6 min walk distance from baseline to 12 months.Change in transcriptomic profiles from baseline to 12 weeks.Change in home handheld spirometry values from baseline to 12 weeks.

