#### Study regimen

Both cases and IPF controls will undertake the same investigations. Following informed consent, the following test results, previously carried out as part of the participant’s usual NHS care, will be used for the purposes of the study:

HRCT findings.Blood results.Lung function tests.Bronchoscopy samples if already taken.

All participants will have baseline investigations at the first visit having provided informed consent. At the first visit, 40 mL of blood will be obtained, full lung function tests and a 6 min walk test will be performed. Participants will also be asked to complete QoL Questionnaires (Medical Research Council Dyspnoea Scale,^20^ Leicester Cough Questionnaire,^21^ IPF-abridged Profile for Assessment and Referral to Care,^22^ King’s Brief ILD Questionnaire^23^ and EQ-5D-5L).^24^ If consent is given for optional bronchoscopy, this will be subsequently performed and bronchoalveolar lavage carried out. Participants with a smartphone will be given the option of a home handheld spirometer and asked to provide daily FVC readings for the first 3 months of the study period.

Further visits at 3 months, 12 months and 24 months will include further 40 mL blood sampling, QoL and full lung function analysis. At 12 months and 24 months a 6 min walk test will be repeated (figure 1).

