#### Details of spirometry

A secondary objective of this study is to determine whether change in daily home (domiciliary) handheld spirometry values over 3 months can predict disease progression and overall survival.

Participants wishing to take part in home spirometry will be provided with a portable handheld spirometer (MIR Spirobank Smart) linked to an electronic health journal (patientMpower smartphone application) on enrolment. Participants will be trained to undertake daily spirometry readings (one forced expiratory manoeuvre/day; seated) for the first 3 months of the study period. All spirometry readings will be blinded to participants and automatically uploaded to patientMpower via the smartphone application, ensuring full encryption throughout. Participants will therefore need to possess, and be confident in using, a smartphone device and have an email address. The spirometry data will then be transferred to the University of Nottingham for further analysis. Participants will be able to continue to use the spirometer and patientMpower application with open display of FVC readings after the initial 3-month observation period if they wish.

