#### Statistics

The primary end point of disease progression (10% relative FVC decline or death within 12 months) will be used dichotomously across all subgroups collectively analysed together, with the exception of IPF controls. Association of baseline biomarker levels with dichotomous disease progression and overall survival will be analysed using binomial family of generalised linear models, while Gaussian family or otherwise appropriate models will be used to assess associations with continuous secondary end points. The Benjamini-Hochberg procedure will be applied to account for multiplicity as appropriate. Repeated measures mixed models will be used to assess associations over time, which includes time points within one model and circumvents correction for multiple testing. Fixed factors will include baseline demographic information. Where putative biomarkers are identified, end point data will be used to compare biomarker levels by time-to-event through proportional hazard models; comparable ability to predict end points will be assessed through sensitivity and specificity analyses (receiver operator characteristic curves).

To identify transcriptomic biomarkers, RNA-seq libraries will be prepared and entered into a workflow for read count normalisation enabling quantification of transcript expression; normalisation ensures length and abundance of cDNA reads are corrected according to other genes (reads per kilobase per million) and further library scaling can occur.^25 26^ Libraries, aligned to an appropriate reference genome, will enable detection of differential gene expression and SNPs/variants according to primary end point and secondary measures of disease severity. Transcript-discovery artefacts, transcripts that remain below detectable levels of change across compared samples, as well as any with zero mapped reads will be excluded. R statistical packages will be used for these bioinformatics workflows.

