Further statistical analyses will be performed to determine associations between identified biomarkers and exploratory secondary objectives. Statistical approaches include, but are not limited to, correlation and analyses of variance between biomarker levels and patient-reported QoL outcomes or disease exacerbations; machine learning strategies on home spirometry to detect decline in lung function, and subsequent comparison of sensitivity with traditional spirometry measures at predicting end points. Factor analysis approaches will be used to reduce dimensions of data sets and assess clustering; generalised linear models will be used to test associations.

Confounding factors are particularly important in studies that hope to offer causal inference of biomarkers on clinical outcomes,^27^ and corrections to adjust for these will be applied in the analysis as proposed by the directed acyclic graph (figure 2).^28^ Fixed factors in mixed models will include baseline demographic information: age, gender, body mass index and smoking status. Exposure history in patients with chronic HP will be collected as will time from diagnosis to enrolment across all subgroups and adjusted for as a potential confounder. Some participants may be on background therapies such as immunosuppression and corticosteroids. While these therapies are likely to be confounders, it is possible they may decrease or increase progression of fibrosis based on the PANTHER (Prednisone, Azathioprine, and *N*-Acetylcysteine: A Study That Evaluates Response in Idiopathic Pulmonary Fibrosis) Study.^29^ Therefore, models will include treatment strategy as part of the minimal set of adjustment for estimating direct effect on end point. The objectives of the study do not extend to assessing treatment effect. Further unknown confounders will be identified from the spirometry smartphone application that will collect various data such as air quality index to inform limitations and future study.

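### The exploratory comparison of home with traditional spirometry names only sensitivity; it should also fix or match specificity

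*Protocol article*

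**What the plan says.** The Objectives section of the Protocol article lists as a secondary objective: "Investigate whether home handheld spirometry over 3 months predicts disease progression and survival". The primary end point, which is one of the outcomes to be predicted, is dichotomous: "Disease progression defined as relative forced vital capacity decline ≥10% or death within 12 months".

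Two places in the Statistics section bear on how prediction is to be judged:

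- For putative biomarkers, after the proportional hazards step: "comparable ability to predict end points will be assessed through sensitivity and specificity analyses (receiver operator characteristic curves".
- For home spirometry, in a later paragraph, machine learning is to detect decline in lung function, with "subsequent comparison of sensitivity with traditional spirometry measures at predicting end points".

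The second item belongs to a list introduced by "Statistical approaches include, but are not limited to", in a paragraph concerned with "associations between identified biomarkers and exploratory secondary objectives".

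The two kinds of measurement differ in density. Home readings are "one forced expiratory manoeuvre/day; seated", taken over the first 3 months (Details of spirometry). Clinic lung function is measured at the first visit and then on this schedule: "Further visits at 3 months, 12 months and 24 months will include further 40 mL blood sampling, QoL and full lung function analysis" (Study regimen).

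**The concern.** Sensitivity describes a classifier at one cut-off. Moving the cut-off towards flagging more people raises sensitivity and lowers specificity, with no change in how well the underlying measure separates progressive from stable participants. Two measures can be compared on sensitivity only if specificity is fixed or matched, or if the whole ROC curve is used. The home spirometry clause names none of these, although the same section names the right pair of metrics for biomarkers.

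The design gives a reason to care. A machine-learning rule fitted to a dense daily series and a rule based on a change between two clinic visits may well sit at different operating points, and nothing in the clause equalises them. An analysis plan that followed the clause literally could report a difference in sensitivity that reflects the choice of cut-off and not better prediction. The stake is the interpretation of one secondary objective. The primary end point, the sample size and the interim rule do not depend on it.

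**Working it through.** The plan gives no figure for this comparison, so there is nothing to reproduce. The check is a reading of the two Statistics sentences followed by an illustration.

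**Reading**

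| Question | Biomarkers | Home v traditional spirometry |
|---|---|---|
| Metric named | Sensitivity and specificity (ROC) | Sensitivity |
| Specificity, threshold or AUC named | Specificity and ROC | None |
| Scope | Putative biomarkers, once identified | Home spirometry, with machine learning |
| Rule for calling one measure better | None | None |

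**Illustration: same discrimination, different cut-offs**

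Assumption (not in the documents): an equal-variance binormal model. Then

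sensitivity = Φ(√2 · z(AUC) + z(1 − specificity)).

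For an assumed AUC of 0.70, z(0.70) = 0.524 and √2 × 0.524 = 0.742.

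- Specificity 80%: z(0.20) = −0.842, so sensitivity = Φ(0.742 − 0.842) = Φ(−0.100) = 0.460.
- Specificity 50%: z(0.50) = 0, so sensitivity = Φ(0.742) = 0.771.

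The difference is 0.771 − 0.460 = 0.311, or 31 percentage points, from the cut-off alone. Per 100 progressive and 100 stable participants, the looser cut-off finds about 31 more progressors and wrongly flags 30 more stable participants (50 against 20). A comparison of sensitivity shows only the first of these.

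**Range over the assumed AUC**

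| AUC | Spec. 90% | Spec. 80% | Spec. 70% | Spec. 50% |
|---|---|---|---|---|
| 0.60 | 0.178 | 0.314 | 0.434 | 0.640 |
| 0.70 | 0.295 | 0.460 | 0.586 | 0.771 |
| 0.80 | 0.464 | 0.636 | 0.747 | 0.883 |

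The order can even reverse. A measure with AUC 0.60 used at 50% specificity has sensitivity 0.640, marginally above the 0.636 of a measure with AUC 0.80 used at 80% specificity.

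**The case against.** The strongest reply has four parts.

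1. **The list is open and the analysis is exploratory.** This stands. A reader might infer that home and clinic spirometry will be compared on sensitivity and nothing else, so that whichever flags more people wins. The documents do not support that: they do not exclude specificity, and they state no rule for preferring one measure.

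2. **There is no superiority objective.** This also stands. The objective asks whether home spirometry predicts progression and survival. A reader might infer that it could be declared superior, but the article does not set out to declare this.

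3. **ROC analysis is already planned in the same section, and the home spirometry clause may be shorthand for it.** This is possible, and the authors clearly know the method. However, the ROC sentence is conditional on putative biomarkers having been identified, so its extension to home spirometry has to be assumed.

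4. **Thresholds and accuracy measures belong in the full protocol or analysis plan.** For missing detail this is right, and the absence of a threshold would be no finding by itself. Here, though, the article does name a metric, and that metric is not enough if followed as written.

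A further tempting inference is that daily readings must produce more false alarms than a clinic change. The documents do not support this either. They give no flag rule, no within-person variability and no independence assumption. A model using trends or averages over many readings could reduce noise instead. Any false-alarm percentage built on a rule that a single low reading triggers a flag would describe a rule that is not in the plan.

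**Conclusion.** The point holds in a limited form. For the exploratory comparison of home with traditional spirometry, the article names sensitivity only, and its ROC approach is not expressly carried over. Sensitivity at unmatched specificity cannot rank two predictors. Under the binormal assumption, the cut-off alone can move it by 31 points at AUC 0.70 (46% to 77%). These figures show what is possible; they do not estimate what this study would find, since the AUC and both specificities are assumed. With an open list, exploratory status and no decision rule, this is an inexpensive improvement to the wording of a secondary analysis. It has no consequence for the primary analysis.

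**What to change.** Reword the home spirometry clause in Statistics along these lines: *In participants with both measures, the ability of home and traditional spirometry to predict end points will be compared by the paired difference in AUC with its 95% CI. Sensitivity will be compared only at a common specificity (for example 80%). Cross-validated predictions will be used for the machine-learning rule.*

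The restriction to participants with both measures matters because home spirometry is optional and needs a smartphone. Cross-validation keeps the fitted rule from being judged on the data that trained it. If a common specificity is used, fix its value before the analysis so that the operating point is not chosen after seeing the results.

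The cost is one or two sentences and slightly more analysis, with no new data or participants. The downside is that any advantage of home spirometry may look smaller than under an unmatched comparison of sensitivity.

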**Figure 2 F2:**
[figure not shown]
Directed acyclic graph (DAG) illustrates proposed model of causal inference and minimal sufficient adjustment sets (confounders; red) for estimating the direct effect of biomarker expression profiles (exposure; green) on disease progression (outcome; blue). Image generated using DAGitty.net environment. QoL, quality of life. BMI, body mass index; ILD, interstitial lung disease.

### Sample size justification

A power calculation has been conducted using prior data obtained at 3 months in the PROFILE (Prospective Observation of Fibrosis in the Lung Clinical Endpoints) study of patients with IPF.^8^ The study demonstrated that 90 stable and 90 progressive individuals were sufficient to detect a twofold change in MMP7 with >90% power and 5% type I error rate. MMP7 was selected for power calculation as the most conservative of the biomarkers identified in the PROFILE Study, with the lowest threshold for biomarker change and least statistical precision, thus powering on MMP7 ensures that other biomarkers will be analysed with adequate power. The calculation demonstrates that a sample of 100 participants with progressive fibrosis and 100 with stable fibrosis will be large enough to detect dynamic differences in biomarkers over 3 months with 80% power and a type I error rate of 5% (α=0.05). Therefore 200 participants with ILD will be recruited assuming 50% disease progression. Fifty positive IPF controls will be recruited to take part in the study to benchmark progressive fibrotic lung disease but will not be included in the final analysis.

The study is also appropriately powered for genetic risk scores. An individual SNP with 25% minor allele frequency would have >70% power to detect an OR of 1.8 for stable versus progressive disease. The power for a risk score comprising multiple variants is expected to be greater. This assumes an additive genetic model, p<0.05, in 100 stable versus 100 progressive patients whereby with each additional marker added to the model the power is actually increased rather than reduced. The markers used will all be defined a priori based on data obtained from the PROFILE Study^7 8^ but are likely to include MUC5B, DSP, AKAP13, SP-D, CA-125, CA19-9, MMP-7, CRPM and C6M.

Following the recruitment of 100 participants who complete 1 year in the study, an interim sample size re-estimation by an independent data monitoring committee will be conducted to determine the progression status between blinded subgroups. If the blinded progression status is approximately 50%, recruitment will continue as described. If however, any subgroups show a relatively stable phenotype they will be excluded from subsequent recruitment, after being unblinded to the data monitoring committee. To attain an adequately powered sample size with 50% progressive fibrosis, further recruitment will be enriched with participants from the progressive phenotypical subgroups relative to rate of progression in interim analysis. Those recruited from subsequently excluded subgroups will be removed from the primary analysis, as they will be sources of inconsistency. However, if all subgroups progress at a substantially lower rate than expected and conditional power calculations at interim analysis suggest futility then all subgroups will be included in an analysis that demonstrates the null hypothesis (fibrotic lung disease progress at a rate specific to aetiology) could not be rejected. The study is not statistically powered to detect differences between ILD subgroups, although exploratory analyses will be carried out to inform future studies and support replication studies.

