### Selection of participants

Two hundred participants with recently diagnosed (within 18 months of study start date) fibrotic lung disease (50 each of rheumatoid-ILD, asbestosis, chronic HP and unclassifiable ILD) and 50 IPF participants as positive controls will be recruited from ILD clinics locally and across the UK. Only participants with MDT confirmed diagnosis of fibrotic ILD with radiological evidence of parenchymal lung fibrosis evidenced by reticulation and traction bronchiectasis, with or without honeycomb change will be recruited. Those with inflammatory radiological changes without evidence of fibrosis will not be deemed suitable regardless of clinical phenotype.

Recruitment will be reviewed on an ongoing basis and should rates fall below the expected levels, additional National Health Service (NHS) sites within the UK will be considered for participation. Eligible patients who meet the inclusion/exclusion criteria will be invited to consent. Most participants will be identified through outpatient clinics, but recruitment will not be restricted to this route. It will be explained to participants that entry into the study is entirely voluntary and that further treatment and care will not be affected by a decision to not partake. It will be clearly stated that participants are free to withdraw from the trial at any time. All participants will provide written informed consent, which will be countersigned by a member of the study team.

Inclusion criteria:

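### If a subgroup looks stable at the interim, its enrolled participants leave the primary analysis, so the analysed aetiologies are chosen on the observed primary outcome

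*Protocol article*

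**What the plan says.** The primary objective (Protocol article, Objectives) is to "Identify biomarkers that determine progressive fibrotic lung disease irrespective of aetiology". The Statistics section says that the primary end point "will be used dichotomously across all subgroups collectively analysed together, with the exception of IPF controls". Selection of participants sets the cohort at "50 each of rheumatoid-ILD, asbestosis, chronic HP and unclassifiable ILD", that is 200 non-IPF participants. Sample size justification compares 100 progressive with 100 stable participants at 80% power: "Therefore 200 participants with ILD will be recruited assuming 50% disease progression".

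The last paragraph of Sample size justification describes an interim review by an independent committee once 100 participants have completed one year. It has three branches:

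- Progression is near 50%: recruitment continues unchanged.
- If "any subgroups show a relatively stable phenotype they will be excluded from subsequent recruitment", later recruitment is weighted towards the progressive subgroups. The next step is: "Those recruited from subsequently excluded subgroups will be removed from the primary analysis, as they will be sources of inconsistency".
- All subgroups progress slowly and conditional power points to futility: all subgroups are analysed.

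The point here concerns the second branch only. That paragraph gives no numerical threshold for stability and no revised total.

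**The concern.** Progression status at one year is the primary outcome. In the second branch it decides which aetiologies enter the primary analysis, and it does so retrospectively for people already enrolled. Three things follow.

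- A positive result would apply to the aetiologies that progressed at the interim. It would say nothing directly about those removed, although the objective is a marker that works whatever the cause.
- The main contrast is progressive against stable, and a stable subgroup supplies mostly stable comparators. The protocol calls these people a source of inconsistency, but they are data that the comparison needs.
- The same section says that the study is not powered for differences between subgroups, yet the rule acts on such differences at half the planned sample.

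**Working it through.** **Inputs.** From the protocol: four non-IPF subgroups of 50; 100 v 100 at 80% power, 5% type I error; SNP with minor allele frequency 0.25, OR 1.8, additive model, p<0.05, stated power >70%; interim at 100 participants. Assumed: the 100 are non-IPF and evenly spread (25 per subgroup), tests are two-sided, the biomarker effect is the same in all subgroups, and retained subgroups progress at 50%.

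**Formulas.** Let I = n1·n0/(n1+n0) for a pooled analysis, or I = Σ n·p·(1−p) over subgroups for a stratified one.

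- SNP power = Φ(√(I × 2 × 0.25 × 0.75) × ln 1.8 − 1.96).
- Biomarker power = Φ(d√I − 1.96).

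**The plan's own figures.** At 100 v 100, I = 50. SNP power = Φ(√18.75 × 0.588 − 1.96) = 72.1%, which agrees with the stated >70%. The biomarker calculation gives no SD or standardised effect, so d is solved from its 80%: d = (1.96 + 0.842) × √(2/100) = 0.396.

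**Chance of a false drop.** With 25 people at a true 50%, the standard error is √(0.25/25) = 10 points. The chance that at least one of four subgroups falls at or below a cut-off is 1 − (1 − P)^4, with P from Binomial(25, 0.5):

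- 9/25 (36%) or fewer: P = 11.5%, at least one 38.6%
- 8/25 (32%) or fewer: P = 5.4%, at least one 19.9%
- 7/25 (28%) or fewer: P = 2.2%, at least one 8.4%

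The cut-offs are illustrative, since the protocol gives none.

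**Power with total recruitment held at 200.** Ranges are for dropped subgroups progressing at 10% to 30%. Fifty are affected if two subgroups of 25 are dropped, or one of 50 when all 200 are already enrolled.

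| Case | I | Biomarker | SNP |
|---|---|---|---|
| 100 v 100 as planned | 50 | 80.0% | 72.1% |
| 25 deleted (87.5 v 87.5) | 43.75 | 74.6% | 66.3% |
| Same 25 kept, pooled | 49.5–49.9 | 79.6–79.9% | 71.6–72.0% |
| Same 25 kept, stratified | 46.0–49.0 | 76.6–79.2% | 68.5–71.2% |
| 50 deleted (75 v 75) | 37.5 | 67.9% | 59.6% |
| Same 50 kept, pooled | 48.0–49.5 | 78.4–79.6% | 70.3–71.6% |
| Same 50 kept, stratified | 42.0–48.0 | 72.8–78.4% | 64.5–70.3% |

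The direction does not depend on the scenario. Adding people to either group raises n1·n0/(n1+n0), and each subgroup adds a positive term to Σ n·p·(1−p). Under a common effect, keeping given participants therefore always beats deleting them.

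**Comparators lost.** With three subgroups of 50 at 50% and one at 20%, stable participants number 75 + 40 = 115. Deleting the slow subgroup removes 40 of them (40/115 = 35%).

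**The case against.** **The loss of power is conditional.** A reader might infer that the rule always lowers power. The text does not support that. It applies in one of three branches, it is called a sample size re-estimation, and it aims at an adequately powered sample without capping the total at 200. Recruiting 225 or 250 to analyse 200 would restore 80%. This stands, although the removed participants would still be wasted.

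**The figures depend on the effect chosen.** The same section says that "90 stable and 90 progressive individuals were sufficient to detect a twofold change in MMP7 with >90% power and 5% type I error rate". Solving from 90% at 90 v 90 gives d = 0.483, and 75 v 75 then has 84% power, above target. This also stands. The fall to 68% belongs to the 80% statement, but keeping participants is better under either effect.

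**Enrichment has value.** Relative to 50%, the information per person, 4p(1−p), is 64% at 20% progression but only 36% at 10%. Against no adaptation at all, and with stratification, the whole rule does slightly better when dropped subgroups progress at 10%: 74.6% v 72.8% for one, 67.9% v 63.7% for two. That gain comes from redirecting recruitment. Redirecting and also keeping those enrolled gives 76.6% and 72.8%.

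**The effect may differ by aetiology.** Deletion could help if the marker effect is absent in stable aetiologies. That heterogeneity is what the objective needs examined, so it is a weak reason for removing the evidence.

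**Validity within the retained set.** A reader might infer inflated predictive values or type I error. The Statistics section plans sensitivity, specificity and ROC curves, which do not depend directly on prevalence. Choosing whole aetiologies on progression, without reference to the biomarker, does not by itself bias the association among those retained.

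**The objective is not wholly defeated.** Dropping one aetiology leaves three pooled, with about half their participants stable, and exploratory subgroup analyses remain. The pooled-analysis statement could be read as the default and the interim rule as its pre-specified exception, but the article does not say so.

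**Conclusion.** The point holds for the second interim branch. Removing enrolled participants because their aetiology looked stable on the primary outcome conflicts with the pooled primary analysis. It narrows the conclusion to aetiologies that progressed at the interim, and it discards comparators. The rule can act on chance: 39%, 20% or 8% at the three illustrative cut-offs, assuming 25 per subgroup. A threshold may exist in a plan not shown, and the finding does not rest on its absence.

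Under a common effect, deletion is always worse than retention. The absolute fall, to about 75% or 68% for the biomarker and 66% or 60% for the SNP, holds only if recruitment stays at 200. The biomarker figures also assume an effect sized for 80% at 100 v 100. The finding does not extend to an unconditional loss of power, to bias in the planned accuracy measures, or to complete failure of the objective.

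**What to change.** - Delete the sentence that removes participants of excluded subgroups from the primary analysis.
- State that every enrolled non-IPF participant stays in that analysis, with aetiology as a stratum or fixed effect.
- Let the interim change only the proportions recruited afterwards.
- Report the analysis restricted to retained subgroups as a sensitivity analysis, with progression rates by subgroup.

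The cost is protocol wording. The final progression proportion may fall below 50%. For example, with 25 kept at 20%, it is (87.5 + 5)/200 = 46%, and biomarker power is 79.8% pooled or 78.2% stratified, against 74.6% with deletion. That small loss of efficiency is less than the loss from removing the participants.
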